#### Newly formed gallstones/sludge on ultrasound in patients on ultrasound at 24 months

In patients without gallstones at baseline, the total number of patients with newly formed gallstones on ultrasound at 24 months will be reported. The chi-squared test results and preferred measure for effect size will be shown in Table 2.

#### The number of and time to cholecystectomies

The total number of patients with cholecystectomies in both study arms will be reported. Whether a patient underwent a cholecystectomy is registered by an investigator in the case report form and verified at the 24-month follow-up. The chi-squared test will be used to compare the outcomes between the study arms. The time to cholecystectomy will be compared using Kaplan-Meier survival analysis. The number of cholecystectomies and preferred effect size will be shown in Table 2, and the outcome of the Kaplan-Meier survival will be provided in the text.

#### Therapy compliance

Therapy compliance is measured in three ways. Patients are asked for therapy compliance at their 6-month follow-up appointment to indicate how many days per week they took the trial medication. Secondly, patients are asked to return the package material of the trial medication that was taken together with any leftovers of the trial medication. Consequently, a pill count is performed by the clinician. Furthermore, patients have to complete an online questionnaire about trial medication adherence 6 weeks and 6 months after surgery. The questionnaire consists of a modified eight-item Morisky Medication Adherence Scale. Questions address the method of taking the trial medication, difficulties in taking the trial medication, potential solutions for taking the trial medication and the reason for discontinuing the trial medication prematurely. Therapy compliance will be defined in 5 categories: did not use trial medication, poor (< 91 pills (25%)), moderate (< 300 pills (< 80%)), good (≥ 300 pills (> 80%)) and complete therapy (all pills = 364 (100%)). The Mantel-Haenszel chi-squared test will be used to compare therapy compliance of UDCA and placebo, and the outcome will be shown in a secondary outcome table (Table 3). The evaluation of the questionnaires about the trial medication will not be included in this SAP and primary paper.

**Table 3 Tab3:** Therapy compliance, side effects and SAEs

	UDCA (***n***=)	Placebo (***n***=)	***p***
**Therapy compliance**—*n* (% *n*/*N*)			
Did not start trial medication			
Poor (< 91 pills)			
Moderate (< 300 pills)			
Good (≥ 300 pills)			
Complete therapy (364; all pills)			
**Side effects of treatment (AEs)**—*n* (% *n*/*N*)			
Diarrhoea			
Abdominal pain			
Skin rash			
**SAEs**—*n* (% *n*/*N*)			
Related to trial medication			
Not related to trial medication			

#### Quality of life and health utility

The 36-Item Short Form Health Survey and/or RAND 36-item Health Survey will be used to gather information on patients’ health-related quality of life status at baseline and 12 and 24 months. These questionnaires are gathered during regular follow-up of bariatric patients independent of participation in a trial. To minimise the burden of participation in the UPGRADE trial, these questionnaires were not administered doubly. Hence, changes in quality of life will only be reported and provided in a supplementary appendix for a convenience sample of measurements. The EQ-5D-5L will be used to gather information on patients’ health utility at baseline and 3, 6, 12, 18 and 24 months. Based on the EQ-5D-5L scoring profiles, utility scores over time will be derived from a readily available scoring algorithm for the Netherlands [8]. The follow-up data will be assessed by repeated measurement analysis with baseline data as a covariate, using a generalised linear mixed model based on the observed correlation matrix amongst successive measurements. The baseline health utility score will be provided in the baseline table, and the utility scores over time will be displayed per treatment arm in a figure (Fig. 3; with baseline data included for reference).

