### Patient replacement and handling of missing data

Patients not fulfilling eligibility criteria resulting in the exclusion of the ITT analysis will be replaced. If outcome data cannot be obtained by a study follow-up visit at the outpatient clinic, the patient will be contacted by telephone to gather primary and most secondary outcome data. The postoperative ultrasound of these patients and all data on patients that cannot be contacted will be considered missing. For missing data, a multiple (% of missing data) imputation approach will be selected and justified at the time of analysis, based on the observed missing data pattern and using relevant patient characteristics and outcome predictors. The imputed values will be primarily estimated within the observed data ranges. We will not impute missing values if the percentage missing is below 2. If the missing data appear not missing at random, a worse- and best-case scenario will be run, in which all patients lost to follow-up in the placebo arm are considered free of symptomatic gallstone disease, and all patients lost to follow-up in the UDCA arm are considered not free of symptomatic gallstone disease, and vice versa. Missing values of baseline characteristics will not be imputed. Mixed effects modelling will be applied for the analysis of repeated measures from questionnaire data, thereby simultaneously accounting for missing data.

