### Baseline characteristics

The following characteristics of patients will be shown per treatment arm in a baseline table (Table 1): age (years), sex (% F), ethnicity, weight at baseline and at time of surgery (kg), body mass index (BMI) (kg/m^2^) at baseline, hypertension (% yes), dyslipidaemia (% yes), type 2 diabetes (% yes), pain syndrome (% yes), history of abdominal surgery (% yes), medication prior to surgery (% statins, birth control pills, oestrogens), preoperative cholecystolithiasis (% yes), type of surgery (% RYGB), baseline health utility score (derived from the EuroQol 5 Dimensions 5 Level (EQ-5D-5L) questionnaire and the corresponding Dutch scoring algorithm for observed health status profiles) [8]. Categorical variables will be summarised as the proportion of patients with the count divided by the total number of evaluated patients. Continuous variables with a normal distribution will be summarised using means and standard deviations, whereas medians and interquartile ranges will be used in case of non-normal distributions. For continuous variables, a footnote will be added to show the number of evaluated patients. Differences between the study arms will be analysed using the chi-squared test, independent *t* test or Mann-Whitney test and reported at the discretion of the publishing journal’s policy regarding significance testing in baseline tables for RCTs.

**Table 1 Tab1:** Baseline characteristics

	UDCA (***n***=)	Placebo (***n***=)
**Age**—years, mean (SD)		
**Sex**—F, *n* (% *n*/*N*)		

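### Baseline utility enters the mixed model as a covariate but missing baseline values are not imputed, so patients without a baseline score lose all their follow-up utilities

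*SAP article*

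**What the plan says.** The section Quality of life and health utility sets the measurement times: "The EQ-5D-5L will be used to gather information on patients’ health utility at baseline and 3, 6, 12, 18 and 24 months". That is one baseline and five follow-up assessments. The analysis is then described: "The follow-up data will be assessed by repeated measurement analysis with baseline data as a covariate". As to the type of model, the section goes on to specify the fit as "using a generalised linear mixed model based on the observed correlation matrix amongst successive measurements". Baseline values also appear in the planned figure of utilities over time, but only "with baseline data included for reference". Baseline is thus a predictor in the model and not one of the modelled responses.

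The section Baseline characteristics includes in its list the "baseline health utility score (derived from the EuroQol 5 Dimensions 5 Level (EQ-5D-5L) questionnaire", and Table 1 has a row for it.

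The section Patient replacement and handling of missing data gives two rules, one directly after the other. The first is: "Missing values of baseline characteristics will not be imputed". The second is: "Mixed effects modelling will be applied for the analysis of repeated measures from questionnaire data, thereby simultaneously accounting for missing data". No section says what happens to a patient who has follow-up utilities but no baseline score.

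**The concern.** Each rule is ordinary on its own, but together they do not fit. A likelihood-based mixed model copes with missing responses under missing at random: a patient who misses a visit still contributes the visits that were observed. It has no such mechanism for a missing predictor. Baseline utility is constant within a patient, so one absent form makes the covariate missing on every row for that patient, and all the rows leave the analysis.

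The utility comparison then becomes a complete-case analysis with respect to baseline. Randomised patients with observed outcomes are left out, and precision is lost that could be kept at no cost. A reader who relies on the plan's missing-data sentence would not expect this.

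**Working it through.** The plan gives no figure on this point, so there is nothing to reproduce. The check has two parts.

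**1. Does the exclusion follow from the text?**

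- Baseline is a covariate (Quality of life and health utility).
- The baseline utility score is a baseline characteristic (Baseline characteristics, Table 1).
- Missing baseline characteristics are not imputed, with no limit to a table or an analysis (Patient replacement and handling of missing data).
- No other rule covers a missing baseline covariate.

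Taken literally, these leave standard software with a missing predictor and no instruction, and the rows are dropped.

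The mechanism was confirmed by simulation. All settings are assumptions: 900 patients, five follow-up visits, SD 0.2, within-patient correlation 0.5, baseline missing completely at random.

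| Nominal share without baseline | Patients used, baseline as covariate | Observed follow-up records discarded | Patients used, baseline as response |
|---|---|---|---|
| 5% | 845 | 275 | 900 |
| 10% | 821 | 395 | 900 |
| 20% | 733 | 835 | 900 |

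The discarded records are five per lost patient, for example (900 − 821) × 5 = 395.

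**2. How much precision could be kept?**

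Let m be the share without a baseline score and r the correlation of baseline with the follow-up quantity analysed. Neither is in the document. I take m = 5%, 10% and 20%, and a correlation of 0.5 between any two visits.

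The crude factor 1/√(1 − m) gives 1.026, 1.054 and 1.118. It compares the complete cases with a trial in which every baseline score was observed. No analysis can recover scores that were never collected, so it overstates the avoidable loss.

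A patient with follow-up but no baseline contributes an unadjusted value, worth about (1 − r²) of a patient with both. The avoidable inflation is therefore

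SE(complete cases) / SE(all patients) = √{[(1 − m) + m(1 − r²)] / (1 − m)} = √{(1 − m r²) / (1 − m)}.

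*Single visit*, r² = 0.5² = 0.25:

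- m = 5%: √(0.9875/0.95) = 1.020
- m = 10%: √(0.975/0.90) = 1.041
- m = 20%: √(0.95/0.80) = 1.090

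*Average of the five visits*. The variance of the average, relative to one visit, is (1 + 4 × 0.5)/5 = 0.6, so r² = 0.25/0.6 = 0.417:

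- m = 5%: √(0.9792/0.95) = 1.015
- m = 10%: √(0.9583/0.90) = 1.032
- m = 20%: √(0.9167/0.80) = 1.070

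These figures apply to modelling baseline as a response. Filling the covariate with the overall mean recovers somewhat less, because patients with and without a true baseline then share one residual variance. The ratio becomes √{(1 − r²) / [(1 − m)((1 − m)(1 − r²) + m)]}. At m = 20% this is √(0.75/0.64) = 1.083 for a single visit and √(0.5833/0.5333) = 1.046 for the average.

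**The case against.** **The no-imputation rule may be meant only for Table 1.** It uses the heading of the section that describes that table, and the plan nowhere says that patients will be dropped. This may well be the intent. But the sentence stands among the analysis rules and carries no limit, and nothing else covers the covariate. The objection shows how small the repair is, not that none is needed.

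**The missing-data sentence is correct for what it covers.** This stands in part. Follow-up scores are the repeated measures being modelled, and for them the sentence holds under missing at random. It is incomplete, not false: it fails only for a missing baseline score.

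**Baseline as a covariate is standard practice.** True, and the choice need not change. What is missing is a workable rule for patients who lack the covariate.

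**The loss may be trivial.** It may be. The separate count in the Table 1 row for this score does not show how many are missing, since the plan promises the number evaluated for continuous variables generally.

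A reader might also infer two stronger points that the document does not support.

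- *The arm comparison is biased.* In a randomised, double-blind trial, absence of a baseline form should be unrelated to arm. Dropping those patients then costs precision and changes who is represented, but does not by itself bias the comparison among those kept. The plan contains no mechanism that would.
- *The rule also blocks imputation of the primary outcome.* The plan fixes no list of predictors for that imputation; the approach is to be chosen and justified at the time of analysis. Predictors known for every patient can be used, such as the two stratification factors, and nothing requires the baseline utility. The primary chi-squared test uses no covariate.

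**Conclusion.** The point holds for the health-utility analysis. Following the plan as written, with standard fitting, removes every follow-up utility of a patient who has no baseline score, and no other rule in the document prevents this. The consequence is avoidable loss of precision and a departure from the all-randomised set, limited to one secondary outcome.

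The size is unknown because the share of missing baseline scores is not stated. Over the assumed 5% to 20% missing, with an assumed correlation of 0.5, the avoidable increase in standard error runs from about 2% to 9% for a single visit and from about 1.5% to 7% for the five-visit average. At low missingness it is negligible. The change is still worth making, because the remedy costs nothing and makes the missing-data statement true for baseline as well as follow-up.

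**What to change.** Choose one of two options and write it into Quality of life and health utility:

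1. Put the baseline utility in the response vector with the five follow-up values, with a common baseline mean for both arms and arm-by-visit effects after baseline. Every patient with at least one utility value then contributes.
2. Keep baseline as a covariate and fill a missing value with the overall mean, ignoring arm. This also keeps every patient with follow-up data, with slightly less gain in precision.

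In Patient replacement and handling of missing data, limit the no-imputation rule to the descriptive baseline table. State that the mixed model addresses missing follow-up scores, and refer to the chosen rule for missing baseline scores. Report the number of patients per arm who enter the utility model.

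The cost is a few sentences in the SAP. No new data are needed, the analysis stays within a mixed model that SPSS can fit, and the choice can be made before the randomisation code is broken.

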**Fig. 3 Fig3:**
[figure not shown]
Example health utility scores over time

#### Cost-effectiveness, cost-utility and budget impact analyses

The economic evaluation of prophylactic UDCA use after bariatric surgery will be performed as cost-effectiveness analyses and cost-utility analyses from a societal perspective with the costs per patient without symptomatic gallstone disease and the costs per quality-adjusted life year as primary economic outcomes. Also, a budget impact analysis from a governmental, insurer and health care provider perspective will be performed describing the financial consequences of prophylactic use of UDCA and reduced number of surgical interventions for the health care budgets of intramural specialised care, extramural use of drugs, general practitioner care and paramedic care. The economic evaluation will not be included in this SAP.

### Assessment and analysis of safety outcomes and side effects

Safety outcomes are AEs, SAEs and SUSARs. Because AEs are very common after bariatric surgery, we only recorded the AE if there was a reasonable suspicion of the AE being an effect of the trial medication and in case the AE was graded at least as moderately severe or mildly severe lasting longer than 1 week (Table 3). SAEs after bariatric surgery are relatively common as well, so only SAEs that occurred after the start of the trial medication were recorded (Table 3). The number of trial medication-related SAEs and the number of SAEs that were not related to the trial medication will be provided in Table 3. The chi-squared test will be used to compare the safety outcomes between the treatment arms attributable to the trial medication.

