## Statistical analysis plan

### General principles

The randomisation code will not be broken until the last patient reaches 24 months of follow-up, all primary endpoints are reviewed by a blinded independent endpoint adjudication committee, and data cleaning is completed. The analyses will be performed after data verification and validation have been carried out and after this SAP has been accepted for publication. Analyses will be done by the investigators and biostatistician of the UPGRADE study group, using the most recent version of the SPSS statistical software at the time of analysis. All statistical tests will use a two-sided *p* value of 0.05, and two-sided 95% confidence intervals will be presented for all estimates.

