### Assessment and analysis of primary outcome

The primary outcome is the proportion of patients with symptomatic gallstone disease within 24 months of follow-up. Symptomatic gallstone disease is defined as a biliary disease (biliary pancreatitis, acute cholecystitis, choledocholithiasis, cholangitis or biliary colics) for which a hospital visit or admission was required. To assess the primary outcome, follow-up appointments are held at 6 and 16 weeks, and 6, 12 and 24 months by one of the blinded investigators. All primary endpoints will be reviewed by a blinded independent endpoint adjudication committee.

To provide an estimator of the effectiveness of UDCA, we will perform a standard ITT analysis. The difference between outcomes by study arm will be compared using the chi-squared test with a risk ratio (unless editors of the accepting journal suggest to report odds ratio) as an indicator for effect size, as shown in Table 2. The results of the mITT and other data sets will be provided in a supplementary appendix, if no contradictory findings are to be reported.

**Table 2 Tab2:** Gallstone-related outcomes

	UDCA (***n***=)	Placebo (***n***=)	Effect size	***p***
*Primary outcome*				
**Symptomatic gallstone disease**—*n* (% *n*/*N*)				
Biliary pancreatitis				
Acute cholecystitis				
Choledocholithiasis				
Cholangitis				
Biliary colic				
*Secondary outcomes*				
**Presence of gallstones/sludge on ultrasound at 24 months**—*n* (% *n*/*N*)				
**Newly formed gallstones/sludge on ultrasound at 24 months**—*n* (% *n*/*N*)				
**Cholecystectomy**—*n* (% *n*/*N*)				

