We are aware that many studies have reported poor compliance of UDCA after bariatric surgery. Consequently, there is a chance that the expected attrition rate will be exceeded. If this is the case, we assume that we will not need a higher number of patients to assure the availability of sufficient evaluable patients, because the relative reduction is probably larger than the 50% reduction used in the power analysis.

In our trial, the postoperative ultrasound is performed during a regular follow-up visit at the outpatient clinic. Due to the unforeseen and unique bankruptcy of two participating centres, and the coronavirus disease (COVID-19) pandemic, the regular follow-up schedule was suspended temporarily. Therefore, we decided to maintain a relatively large window (18 to 30 months) in which the postoperative ultrasound—originally scheduled at 24 months—has to be carried out. We will explore whether the contrast between the two study arms is stable across different time frames in order to assess the impact of the logistic artefact.

The results of the UPGRADE trial will optimise the postoperative management of bariatric patients and probably lead to a reduction of patients with symptomatic gallstone disease. This trial has the potential to affect daily clinical practice and improve patient outcomes. Second, cost-effectiveness, cost-utility and budget impact analyses of postoperative UDCA prophylaxis may demonstrate the societal value of prophylactic UDCA treatment for health care providers, insurers and taxpayers.

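### Harms get per-arm counts and a chi-squared p value but no named between-arm estimate, so the SAP's confidence-interval rule does not clearly reach them

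*SAP article*

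**What the plan says.** The SAP section on safety outcomes and side effects names one between-arm method: "The chi-squared test will be used to compare the safety outcomes between the treatment arms attributable to the trial medication". It names no effect measure. The results go into Table 3, titled "Therapy compliance, side effects and SAEs", whose columns are UDCA, placebo and p. The rows carry counts and percentages per arm, for example "Side effects of treatment (AEs)—*n* (% *n*/*N".

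The efficacy side is handled differently. The rule for the primary outcome reads: "compared using the chi-squared test with a risk ratio (unless editors of the accepting journal suggest to report odds ratio) as an indicator for effect". Table 2 has a column for this measure. The sections on ultrasound findings and cholecystectomy also refer to a preferred effect measure shown in Table 2.

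The General principles section sets a rule for the whole plan: "All statistical tests will use a two-sided *p* value of 0.05, and two-sided 95% confidence intervals will be presented for all estimates".

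**The concern.** For the binary gallstone outcomes the plan both estimates and tests. For harms it only tests. The confidence-interval rule is tied to estimates, and with no between-arm safety estimate defined it has nothing definite to act on.

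UDCA is being tested as prophylaxis. By the SAP's own background figure of 8–15% with symptomatic disease within 24 months, 85–92% of patients would not have the event. The benefit–harm judgement therefore depends on how large an excess of harm the data can exclude. A p value does not answer that, whereas an interval for the risk difference does. The recording rule for AEs (suspected drug effect, and at least moderate or mild for more than a week) reduces the counts, which makes a non-significant result less informative still.

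**Working it through.** **1. The texts side by side**

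| | Gallstone outcomes | Side effects and SAEs |
|---|---|---|
| Test | chi-squared | chi-squared |
| Effect measure named | risk ratio (odds ratio if editors ask) or preferred measure | none |
| Table columns | UDCA, placebo, effect size, p | UDCA, placebo, p |
| Does the 95% CI rule apply? | yes, to the named estimate | unclear, as no between-arm estimate is named |

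**2. Assumed sample sizes**

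The SAP refers to the protocol for its sample size, so there is no figure to reproduce. To bracket n per arm I took a control rate p₁ of 8–15% (background incidence in the Abstract and Introduction), p₂ = p₁/2 (the 50% reduction mentioned in the Discussion), two-sided α = 0.05, 1:1 allocation, and an assumed power of 80% or 90% with no dropout allowance:

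n = [1.96·√(2p̄(1−p̄)) + z_β·√(p₁(1−p₁) + p₂(1−p₂))]² / (p₁−p₂)², where p̄ = (p₁+p₂)/2.

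- 8% v 4%, 80%: (1.96·√0.1128 + 0.842·√0.1120)² / 0.0016 = 553
- 8% v 4%, 90%: 739
- 15% v 7.5%, 80%: 278
- 15% v 7.5%, 90%: 371

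I used 280, 450, 550 and 750 per arm. The use of 8–15% as the control rate is my assumption. The SAP ties only the 50% reduction to the power analysis.

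**3. Chance of missing a true doubling of harm**

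I enumerated both binomial distributions exactly and applied the uncorrected Pearson test at two-sided 0.05. A miss is any result that is not a significant excess on UDCA. The harm rates are assumed, because the SAP gives none.

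| True rates, placebo to UDCA | 280 | 450 | 550 | 750 |
|---|---|---|---|---|
| 1% to 2% | 85% | 78% | 73% | 64% |
| 2% to 4% | 72% | 58% | 50% | 37% |
| 3% to 6% | 60% | 41% | 32% | 19% |
| 5% to 10% | 38% | 18% | 11% | 4% |

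By the normal approximation, power for a doubling reaches 50% at 1,136 per arm (control rate 1%), 559 (2%), 367 (3%) and 214 (5%).

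**4. What an interval adds**

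Take an assumed result of 14/450 on UDCA and 7/450 on placebo. Table 3 as laid out would print 3.1%, 1.6% and a p value.

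- Risk difference: 7/450 = 1.56 percentage points.
- Chi-squared: pooled rate 21/900 = 0.0233; 0.01556² / (0.0233 × 0.9767 × 2/450) = 2.39; p = 0.12.
- Risk ratio: 2.0; SE of the log = √(1/14 + 1/7 − 2/450) = 0.458; 95% CI 0.8 to 4.9.
- 95% CI for the risk difference: Wald −0.4 to 3.5 points; score −0.5 to 3.8 points.

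The result is not significant, yet it does not exclude an excess of nearly 4 per 100 patients. The p value does not convey that.

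**The case against.** The strongest reply has four parts.

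- **No misreading is planned.** A reader might infer that the SAP intends to treat p > 0.05 as absence of harm. No sentence says so, and the SAP sets no rule for interpreting safety. This stands: over-reading is a foreseeable risk of a table without estimates, not an error the plan commits.
- **The p value is not alone.** Table 3 prints counts, denominators and percentages, from which any reader can compute a risk difference and its interval. This stands as a fact. But the plan does not leave the gallstone outcomes to the reader, and there is no stated reason to do so for harms.
- **The General principles rule may already cover safety.** Table 2 has no separate confidence-interval column either, yet the rule plainly covers its estimates. So the lack of such a column in Table 3 does not by itself show that intervals are excluded. This stands in part. The difference is that Table 2 has a named estimate for the rule to act on, and Table 3 has none.
- **Low power for uncommon harms is common to trials sized on efficacy, and the rates here are assumed.** This also stands. A reader might infer that a doubling of harm would usually be missed. That holds at about 1% across the whole bracket and at 2% up to roughly 550 per arm. It is mixed at 3% and does not hold at 5%. The bracket also leaves out dropout: the Discussion mentions an expected attrition rate, and a larger recruited number would lower the miss rates. An added interval does not raise power; it shows how imprecise the comparison is.

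**Conclusion.** The concern holds as a gap in the specification. Safety has per-arm n (%) and a p value but no named between-arm estimate, in contrast to the gallstone outcomes, and the confidence-interval rule therefore does not clearly reach harms. A non-significant safety result could be over-read. How much that matters depends on the harm rate and the sample size: misses of 64–85% at 1% to 2%, 37–72% at 2% to 4%, 19–60% at 3% to 6% and 4–38% at 5% to 10%, all for 280 to 750 per arm. Those sizes and rates are assumptions.

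The documents do not support saying that the plan equates non-significance with safety, or that doublings of harm would generally go undetected. The primary efficacy analysis is unaffected. What is affected is how precisely the trial can state the harm side of its conclusion.

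**What to change.** In the safety section and in Table 3, name the between-arm estimate: the risk difference, UDCA minus placebo, in patients with at least one event, with a two-sided 95% confidence interval by a score method suited to low counts, for each side-effect row and each SAE row. State that safety will be interpreted from the interval and that p > 0.05 will not be reported as absence of harm. The p column may stay, labelled descriptive.

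The change needs SAP wording and one extra table column, from data already collected, and can be made before the randomisation code is broken. The downside is a more cautious safety statement, because the intervals will be wide.
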